### Relationship to Study Intervention

*The clinician’s assessment of an AE's relationship to study intervention is part of the documentation process, but it is not a factor in determining what is or is not reported in the study. If there is any doubt as to whether a clinical observation is an AE, the event should be reported. All AEs must have their relationship to study intervention assessed. In a clinical trial, the study intervention must always be suspect. To help assess, the following guidelines are used:*

- ***Related*** *– The AE is known to occur with the study intervention, there is a reasonable possibility that the study intervention caused the AE, or there is a temporal relationship between the study intervention and event. Reasonable possibility means that there is evidence to suggest a causal relationship between the study intervention and the AE.*
- ***Not Related*** *– There is not a reasonable possibility that the administration of the study intervention caused the event, there is no temporal relationship between the study intervention and event onset, or an alternate etiology has been established.*

### Expectedness

This is a minimal risk study; any potential risks are described earlier (in ‘Risks’ section above). There are no expected AEs or SAEs.

## Time Period and Frequency for Event Assessment and Follow-Up

The occurrence of an AE or SAE may come to the attention of study personnel during study visits and interviews of a study participant presenting for medical care, or upon review by a study monitor. All AEs including local and systemic reactions not meeting the criteria for SAEs will be captured on the appropriate RF. Information to be collected includes event description, time of onset, clinician’s assessment of severity, relationship to study intervention (assessed only by those with the training and authority to make a diagnosis), and time of resolution/stabilization of the event. All AEs occurring while on study must be documented appropriately regardless of relationship. All AEs will be followed to adequate resolution.

Any medical condition that is present at the time that the participant is screened will be considered as baseline and not reported as an AE. However, if the study participant’s condition deteriorates at any time during the study, it will be recorded as an AE. UPs will be recorded in the data collection system throughout the study.

Changes in the severity of an AE will be documented to allow an assessment of the duration of the event at each level of severity to be performed. AEs characterized as intermittent require documentation of onset and duration of each episode.

The PI will record all reportable events with start dates occurring any time after informed consent is obtained until 7 (for non-serious AEs) or 30 days (for SAEs) after the last day of study participation. At each study visit, the investigator will inquire about the occurrence of AE/SAEs since the last visit. Events will be followed for outcome information until resolution or stabilization.

All unresolved adverse events should be followed by the investigator until the events are resolved, the subject is lost to follow-up, or the adverse event is otherwise explained. At the last scheduled visit, the investigator should instruct each subject to report any subsequent event(s) that the subject, or the subject’s personal physician, believes might reasonably be related to participation in this study. The investigator should notify the study sponsor of any death or adverse event occurring at any time after a subject has discontinued or terminated study participation that may reasonably be related to this study.

## Reporting Procedures – Notifying the IRB

### Adverse Event Reporting

At each contact with the subject, the investigator must seek information on adverse events by specific questioning and, as appropriate, by examination. Information on all adverse events should be recorded immediately in the source document, and also in the appropriate adverse event module of the case report form (CRF). All clearly related signs, symptoms, and abnormal diagnostic procedures results should recorded in the source document, though should be grouped under one diagnosis.

All adverse events occurring during the study period must be recorded. The clinical course of each event should be followed until resolution, stabilization, or until it has been determined that the study treatment or participation is not the cause. Serious adverse events that are still ongoing at the end of the study period must be followed up to determine the final outcome. Any serious adverse event that occurs after the study period and is considered to be possibly related to study participation should be recorded and reported immediately.

### Serious Adverse Event Reporting

If the report is supplied as a narrative, the minimum necessary information to be provided at the time of the initial report includes:

| - Study identifier - Study Center - Subject number - A description of the event - Date of onset | - Current status - Whether study treatment was discontinued - The reason why the event is classified as serious - Investigator assessment of the association between the event and study treatment |
| --- | --- |

### Unanticipated Problem Reporting

Incidents or events that meet the OHRP criteria for UPs require the creation and completion of an UP report form. It is the site investigator’s responsibility to report UPs to their IRB and to the DCC/study sponsor. The UP report will include the following information:

- Protocol identifying information: protocol title and number, PI’s name, and the IRB project number;
- A detailed description of the event, incident, experience, or outcome;
- An explanation of the basis for determining that the event, incident, experience, or outcome represents an UP;
- A description of any changes to the protocol or other corrective actions that have been taken or are proposed in response to the UP.

To satisfy the requirement for prompt reporting, UPs will be reported using the following timeline:

- UPs that are SAEs will be reported to the IRB and to the study sponsor within 24-72 hours of the investigator becoming aware of the event.
- Any other UP will be reported to the IRB and to the study sponsor within 2 weeks of the investigator becoming aware of the problem.
- All UPs should be reported to appropriate institutional officials (as required by an institution’s written reporting procedures), the supporting agency head (or designee), and OHRP within 2 weeks of the IR’s receipt of the report of the problem from the investigator.

## Reporting Procedures – Notifying the Study Sponsor

The study clinician will complete a SAE Form within the following timelines:

- All deaths and immediately life-threatening events, whether related or unrelated, will be recorded on the SAE Form and submitted to the DCC/study sponsor within 24 hours of site awareness. See Section 1, Key Roles for contact information.
- Other SAEs regardless of relationship will be submitted to the DCC/study sponsor within 72 hours of site awareness.

All SAEs will be followed until satisfactory resolution or until the site investigator deems the event to be chronic or the adherence to be stable. Other supporting documentation of the event may be requested by the DCC/study sponsor and should be provided as soon as possible.

As a follow-up to the initial report, within the following 48 hours of awareness of the event, the investigator shall provide further information, as applicable, on the unanticipated event or the unanticipated problem in the form of a written narrative. This should include a copy of the completed Unanticipated Problem form, and any other diagnostic information that will assist the understanding of the event. Significant new information on ongoing unanticipated adverse effects shall be provided promptly to the study sponsor.

## Safety Oversight

It is the responsibility of the Principal Investigator to oversee the safety of the study at their site. This safety monitoring will include careful assessment and appropriate reporting of adverse events as noted above, as well as the construction and implementation of a site data safety-monitoring plan. Medical monitoring will include a regular assessment of the number and type of serious adverse events.

The project will establish a Data Safety Monitoring Plan (DSMP) in which adverse events (AEs), serious adverse events (SAEs), and unanticipated problems (UPs) related to participation in the study, if identified, will be documented through a centralized database system, investigated, and followed up. The Principal Investigator (PI), Sub-Investigators (Sub-Is), and Project Manager will be well-versed in the reporting procedures described below. All investigators and staff involved in this project have completed an extensive course and passed a certifying exam on the protection of human subjects in research.

As this is a non-invasive, minimal risk study of a preventive intervention, no predefined stopping rules will be used.

To further protect participants and ensure the collection of high-quality data, a Data Safety Monitoring Board (DSMB) will be established for this proposal. The DSMB will be responsible for monitoring participant safety, monitoring data quality, and evaluating the progress of the study, including reviewing the research protocol and informed consent documents, assessing participant risk versus benefit, reporting to the NICHD as appropriate on the safety and progress of the trial, and making recommendations and resolutions of problems reported by the PI. Members of the DSMB will consist of experts or representatives in the fields of relevant clinical expertise. Members will not have any conflict of interest pertaining to this study. DSMB reports will be submitted to the IRB according to IRB policies and procedures. The members of the DSMB will be determined after the outcome of the grant application has been decided.

***Data Safety Monitoring Board***

Membership and Affiliation

The DSMB will consist of a minimum of three members (including the DSMB Chair) and include, but is not limited to, representatives from pediatrics, clinical trials methodology, and/or other applicable fields. Members will serve on the DSMB for a two-year term and will remain eligible for reappointment upon their term’s conclusion.

Conflicts of Interest

Each DSMB member will sign a Conflict of Interest Statement which includes any other relationship that could be perceived as a conflict of interest related to the study and/or associated with commercial interests pertinent to study objectives.

DSMB Responsibilities

Prior to initiation of the study, a detailed DSMB charter will be created. The DSMB charter will be submitted to the IRB prior to the enrollment of the first subject. The DSMB charter will provide a detailed list of the DSMB responsibilities. These responsibilities include, but are not limited to:

Review the research protocol, informed consent documents and plans for data safety and monitoring;

Recommend subject recruitment be initiated after receipt of a satisfactory protocol;

Evaluate the progress of the trial, including periodic assessments of data quality and timeliness, recruitment, accrual and retention, participant risk versus benefit, performance of the trial sites, and other factors that can affect study outcome;

Consider factors external to the study when relevant information becomes available, such as scientific or therapeutic developments that may have an impact on the safety of the participants or the ethics of the trial;

Review study performance, make recommendations and assist in the resolution of problems reported by the Principal Investigator;

Protect the safety of the study participants, including from the main potential risks of the study:

Violation/loss of confidentiality

Discomfort due to disclosure of sensitive information

Concern regarding identification of child abuse/neglect, domestic violence, or other criminality

Report to IRB and/or NICHD on the safety and progress of the trial;

Make recommendations to the IRB, NICHD, and/or the PI concerning continuation, termination or other modifications of the trial based on the observed beneficial or adverse effects of the treatment under study;

Ensure the confidentiality of the study data and the results of monitoring; and,

Assist the NICHD by commenting on any problems with study conduct, enrollment, sample size, and/or data collection.

Protection of Confidentiality

Investigators will expunge all patient, informant, and provider-level identifiers from the dataset prior to providing it to DSMB members during meetings or in reports. All data and discussions conducted by the DSMB will remain confidential. Participant identities will remain concealed from DSMB members.

Content of DSMB Reports

The study PI will ensure that the DSMB is apprised of all new safety and risk information relevant to the study, and of all protocol amendments. Summary safety data, enrollment data, and other progress reports (e.g. protocol deviations, site monitoring summaries) will be provided to the DSMB prior to its annual meeting and at other times as needed.

In the event of a related SAE, a report containing the study title and number, subject’s ID number, date of signed consent, SAE and date of event, narrative explanation (e.g., subject’s major complaint, brief description of event’s evaluation and disposition, pertinent mental health or behavioral assessments, intervention start date, time of last participation, any prior SAE, the PI’s assessment whether the event was expected, and its relatedness to the study’s intervention) will be provided to the DSMB within 48 hours.

Frequency of Meetings

The DSMB will meet in-person or through teleconference a minimum of once annually to review data related to enrollment progress and trial implementation, and to evaluate the ongoing safety of study subjects. Meetings may be cancelled by the Chair if no clinical study review is required. Additional DSMB meetings may be held if it is determined that more frequent study review is required. A detailed agenda will be provided for each meeting. Reports will be provided to DSMB members via secure methods. Based on these reviews, the DSMB will make recommendations to the PI and/or the NICHD Project Officer concerning the continuation, modification, or termination of the trial. The roles and responsibilities of committee members and meeting procedures will be formally described in a charter.

# Statistical Considerations

## Statistical and Analytical Plans

***Effectiveness Outcomes***

Initial ANOVA and Chi-square tests will be conducted to examine baseline equivalence of randomly assigned groups. Analyses with sex as a biological variable, including moderation and subgroup analyses, will be performed. Covariate entry (e.g., sociodemographics) will be decided based on model fit criteria, and sensitivity analyses will be performed for post-randomization risks.

Missing data and attrition: The research team has expertise in minimizing missing data. In addition, multiple imputation (MI)^160^ will be used to replace item-level data using the rich array of concurrently collected variables and prior responses. If an entire measure/survey is missing, we will use chained equations with lagged (in time) variables^161^ using all available information to build a large set of imputed datasets. Estimates will be combined using Rubin’s rules.^160^ When data are Missing at Random, likelihood-based methods provide unbiased estimates of population parameters even when panels are incomplete. In addition, we will use attrition analyses^162^ to examine whether attrition is related to baseline characteristics.

Tests of hypotheses: In order to examine the added value of HS+VIP in comparison to the standard HS model, we will focus on outcomes related to ERH and ECD where we expect the effects of standard HS to be substantially smaller than the integrated HS+VIP model. Impact analyses at each assessment timepoint will be conducted using ordinary least squares (OLS) regression in an intent-to-treat (ITT) framework, adjusted for baseline sociodemographic covariates. In addition, structural equation models (SEM)^163^ will be used to examine family outcomes over time. This will allow us to examine whether initial levels and trajectories in parent well-being, parent-child interaction, and ECD vary between participants, and whether that variation is explained by assignment to HS+VIP or standard HS.

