# Study Procedures and Schedule

## Study Procedures/Evaluations

**Overall Study Procedures:**

For all parent/child dyads who are enrolled in the RCT, we will administer assessments at baseline, 12 months, and 2 years to measure outcomes (e.g., parenting assets/vulnerabilities, parenting practices/parent-child relationship, child development) and covariates (e.g., socio-demographics, biological risk) for Specific Aims 1 and 2. Assessments will include a combination of parent survey, observation of parent/child, direct assessment of child, and medical record review. In addition, we will conduct two assessments with care providers within the clinic to assess intervention implementation. All assessments will be completed by highly trained research assistants blind to group/intervention status.

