**Assessment Procedures**

Assessments will be conducted at 12M and 24M (critical transition points for both parenting and child development) by highly trained, bilingual research staff, masked to intervention condition, to reduce bias. Assessments will last ~1 hour, in line with prior studies of parents of young children. Assessments will include surveys/questionnaires, observations of parents and children, and direct child assessments.

Outcomes to be assessed via questionnaire include:

|  | | | | | |
| --- | --- | --- | --- | --- | --- |
| **Level** | **Construct** | **Instrument** | **Base-line** | **12M** | **24M** |
| Effectiveness Outcomes | | | | | |
| Parent | **Parent-Child Relationship Quality** | Adult-Child Relationship Scale (*α*=.69-.84)^142^ |  | x | x |
|  | **Responsivity/Cognitive Stimulation** | StimQ Reading, Teaching/Play, Verbal Responsivity (*α*=.88)^143^ |  | x | x |
|  | Stress/Mental Health | Edinburgh Depression Scale (*α*=.77-.86)^144^, Perceived Stress Scale ( *α*=.75-.91);^145^ | x | x | x |
|  | Self-Efficacy | Parenting Self-Agency Measure (*α*=.68-.7)^146^ | x | x | x |
|  | Social Support | General Life Satisfaction (*α*=.91),^147^ Dyadic Adjustment Scale (*α*=.7-.95)^148^ | x | x | x |
|  | Structure | limit-setting, proactive parenting, feeding/sleep/screentime routines,^149^ Socolar Discipline Survey (*α*=.56-.82)^150^ |  | x | x |
|  |  | HealthySteps Parent Feedback Survey^170^ |  | x | x |
|  |  | Parenting Daily Hassles^171^ |  | x | x |
| Child | **Social Competence** | Infant Behavior Questionnaire (*α*=.75-.78),^151^ Brief Infant Toddler Social-Emotional Assessment (*α*=.69-.8)^152^ |  | x |  |
|  |  | Child Behavior Checklist (α=.9-.94)^153^ |  |  | x |
|  | Language & Cognitive Development | Early Social Communication Scale (*α*=.61-.91),^154^  MacArthur-Bates Communicative Development Inventories (*α*=.86);^155^  Dual Language Learners English-Spanish Inventories^172^ |  | x | x |
| Implementation Outcomes (CFIR, RE-AIM, CIHS) | | | | | |
| EBPI Provider (care-team member) | Acceptability | Acceptability of Intervention Measure (AIM; *α*=.89)^158^ |  | x | x |
|  | Appropriateness | Intervention Appropriateness Measure (IAM; *α*=.87)^158^ |  | x | x |
|  | CFIR Domains | Evidence-based Practice Attitudes Scale-36 (*α*=.80),^159^ clinic culture, perceived complexity of intervention, external policies, competence | x | x | x |
|  | Acceptability | Parent satisfaction surveys^117^ |  | x | x |
|  | | | | | |

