### Baseline Descriptive Statistics

Intervention and control groups will be compared at baseline for differences in sociodemographic characteristics, including child gender, parity, maternal education, income, and mental health, using omnibus F-tests, t-tests, and chi-square tests.

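### Unnamed model fit criteria decide the covariates, a second sentence reads as if the set were fixed, and neither includes the outcome's own baseline score where one is collected

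*Protocol*

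**What the plan says.** Section 9.1 of the protocol (Effectiveness Outcomes) deals with covariates twice. Its opening paragraph says "Covariate entry (e.g., sociodemographics) will be decided based on model fit criteria". The paragraph on hypothesis tests says "Impact analyses at each assessment timepoint will be conducted using ordinary least squares (OLS) regression in an intent-to-treat (ITT) framework", and describes these models as "adjusted for baseline sociodemographic covariates". The same paragraph adds structural equation models for outcomes over time.

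Other sections bear on what may count as a covariate:

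- Section 7.1 (Overall Study Procedures) says the assessments will measure "covariates (e.g., socio-demographics, biological risk"), so the examples go beyond sociodemographics. The design description in Section 4.1 says the same.
- Section 9.4.3 (Baseline Descriptive Statistics) counts parental mental health among the sociodemographic characteristics compared between arms, "using omnibus F-tests, t-tests, and chi-square tests".
- The measures table under Assessment Procedures (Section 7.1.1) marks five parent scales at baseline, 12M and 24M: the Edinburgh Depression Scale, the Perceived Stress Scale, the "Parenting Self-Agency Measure", General Life Satisfaction and the Dyadic Adjustment Scale. It marks no baseline for the Adult-Child Relationship Scale, StimQ, the structure measures or any child scale.
- Section 4.2.1 lists parent mental health among the primary endpoints.

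**The concern.** Two things look wrong.

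First, a rule that enters covariates according to fit, with no stated criterion or candidate list, leaves the adjusted effect partly to choices made once outcome data exist. The protocol makes those choices count. Section 9.4.4 runs the same analyses after the 12-month assessments, so models could be settled with 12-month results in view. The mediation section takes forward only mediators that show a significant 12-month effect. The false discovery rate correction works across outcomes, and does nothing about a search over covariate sets within one outcome.

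Second, in a randomised comparison of a scale measured before and after, its baseline value is usually the most useful covariate. For the five parent scales that value is in hand, yet neither covariate sentence commits to using it. What is at stake is precision for parent mental health and the other parent scales, and protection of the impact estimates from avoidable analyst choice.

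**Working it through.** **The two sentences side by side.** The first makes entry depend on fit. The second names a set without conditions. They can be read together, with fit choosing among sociodemographic variables, or apart, with the sociodemographics fixed and fit governing anything else. The text does not say which. Neither reading guarantees the own-baseline score.

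**The plan's own figure.** Inputs from Section 9.5: 500 enrolled, up to 20% attrition, d = .30 and alpha .05. Assumed: a two-sided test and equal arms.

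- Analysed: 500 × (1 − .20) = 400, or 200 per arm.
- Standard error in SD units: √(2/200) = .10.
- Power: Φ(.30/.10 − 1.96) = Φ(1.04) = 85.1% (84.9% with the t distribution).

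The stated power of more than 80% is reproduced.

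**Adding the same scale's baseline score.** With baseline-to-follow-up correlation r, the residual variance is multiplied by 1 − r², so power is Φ(.30/(.10·√(1 − r²)) − 1.96). The protocol gives no value of r; a range is assumed.

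| r (assumed) | 1 − r² | Fall in SE | Power at d = .30 | Equivalent families, 400/(1 − r²) |
|---|---|---|---|---|
| 0 | 1.00 | 0% | 85.1% | 400 |
| .3 | .91 | 4.6% | 88.2% | 440 |
| .4 | .84 | 8.3% | 90.6% | 476 |
| .5 | .75 | 13.4% | 93.4% | 533 |
| .6 | .64 | 20.0% | 96.3% | 625 |
| .7 | .51 | 28.6% | 98.8% | 784 |

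For each r these gains are upper bounds, because other covariates may already explain part of the same variance. They apply only to the five scales with a baseline.

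**Effect of selection on type I error.** A null simulation used 400 families (200 per arm), six independent candidate covariates with coefficients .3, .2, .15, .1, .05 and 0, unit residual SD, all 2⁶ = 64 subsets and 2,000 runs, testing at 5%. The Monte Carlo standard error is √(.05 × .95/2000) ≈ 0.5 points.

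| How the covariates are set | Type I error |
|---|---|
| All six, fixed | 5.2% |
| Best AIC | 5.4% |
| Best BIC | 5.8% |
| Subset with the smallest treatment p-value | 9.8% |

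Selection by a named criterion, applied mechanically, shows no clear inflation. Selection on the treatment result roughly doubles the error rate.

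**The case against.** The strongest reply is that little is wrong. A full covariate list is normally left to the statistical analysis plan, which is not shown. Mechanical selection by fit does almost no harm in the simulation. The additional structural equation models look at initial levels as well as trajectories, so baseline information is not ignored altogether.

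Part of this stands. The absence of a list would not be a finding by itself. The protocol, however, does state a rule: an analysis plan that fixed the covariates would depart from it, and one that followed it would keep the choice open. The structural equation models are additional to the OLS impact analyses and do not settle what those adjust for.

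A reader might infer three stronger things that the documents do not support.

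- *That adjustment is confined to sociodemographics in the narrow sense.* The selection sentence offers them only as an example, Sections 4.1 and 7.1 add biological risk, and Section 9.4.3 places mental health among the sociodemographic characteristics. Baseline depression or stress could therefore enter; the text simply does not secure it.
- *That the main models lose precision.* Section 9.1 directs the hypothesis tests at early relational health and child development, and Section 9.2 frames the hypothesis around parenting practices and relational health. The measures table marks no baseline for those instruments, so there is no own-baseline gain to lose. Section 7.3.2 mentions baseline information on the child's development but names no instrument.
- *That the plan inflates type I error to about 10%.* That requires choosing covariates by the treatment p-value, which the protocol does not say. Nor does it say that selection is repeated for each outcome and visit, or when it happens. The open rule merely fails to exclude these.

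**Conclusion.** The point holds in limited form. The two covariate sentences should be reconciled, the fit-based rule is too open, and the own-baseline score should be written in for the five scales that have one. For those scales, at d = .30 with 400 families, power would go from about 85% to at most about 90%, 93% or 96% for r = .4, .5 or .6. This rests on the assumed correlations, equal arms, a two-sided test and no overlap with other covariates.

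No gain is claimed for the relational health and child development outcomes. The risk to type I error is small under mechanical selection and material only if the treatment result can steer the choice. The sample size statement needs no change.

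**What to change.** In Section 9.1, delete the sentence part that lets model fit decide covariate entry, and expand the OLS sentence to do three things:

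1. Name one common set of covariates, all measured at baseline, for every impact model at both visits.
2. Add the baseline score of the same scale wherever it was collected, which covers the five parent scales.
3. State that the set is fixed before any outcome data are compared by arm, including the 12-month analysis.

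Baseline depression and stress scores may be placed in the common set as prognostic covariates for the relational health and child development outcomes, but without any claimed gain in power, since the protocol gives nothing from which to estimate one.

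The cost is one revised paragraph and a few degrees of freedom out of about 400. The five baseline scores are already scheduled for collection.
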